##### 9-week change in self-reported perceived social support

Perceived social support is an important predictor of positive health outcomes in rehabilitation, [61] and has been linked to improved psychological (e.g., self-confidence), [62–64] and behavioral outcomes (e.g., exercise therapy adherence) [64] after sport-related knee trauma. The Multi-Dimensional Scale of Perceived Support is a 12-item instrument with three subscales designed to measure self-reported perceived support from family, friends, and significant others in general populations [65]. Each item is scored on a 7-point scale. Individual item scores are summed to produce a total score with higher scores indicating higher levels of perceived support. The 16-item Perceived Available Social Support Questionnaire will be used to assess perceived support from the sporting or recreational community [66]. This instrument measures availability of support across four subscales (i.e., emotional, esteem, informational, tangible). Each item is scored on a 5-point scale. Individual item scores are summed to produce a score for each subscale with higher scores indicating higher levels of perceived support.

##### 9-week change in normalized peak knee flexor torque

Hamstring weakness is common after knee trauma, [48] and compounded when the Semitendinosus tendon is used as a graft site for an Anterior Cruciate Ligament (ACL) reconstruction [67, 68]. Isokinetic concentric and eccentric knee flexion torque will be assessed on computerized dynamometer (Biodex, System 4™, Biodex Medical Systems Inc. USA) at 60^o^/sec over 0-100^o^ [50]. The peak torque reached over 3 repetitions will be recorded and normalized to body mass (Nm/kg).

##### 9-week change in normalized peak knee extensor and flexor rate of force development and power

Thigh muscle rate of force development and power have been overlooked components of muscle function, [48] despite compelling emerging evidence that they may be more strongly associated with knee function and symptoms early after injury [69–71] and in persons with OA [72]. Computerized dynamometer (Biodex, System 4™, Biodex Medical Systems Inc. USA) will be used to assess and calculate normalized knee extension and flexion rate of force development (Nm/s) and power (Watts). After completing the protocol for normalized peak concentric knee extension and flexion torque the participants’ knee joint will be fixed in 60 degrees of sagittal plane flexion. The peak values reached over three, 5 s repetitions will be recorded and normalized to body mass (Nm/kg).

##### 9-week change in hop performance

Hop testing is the most commonly used clinical assessment of knee-related functional performance in individuals following knee trauma [73]. The 6-m timed hop is a functional task that challenges dynamic knee stability, [74] and is associated with knee OA 5 years after knee trauma [75]. Participants hop forward with the goal of covering a 6-m distance as quickly as they can. Two practice trials will be completed on each limb, starting with the unaffected side to familiarize participants with the task. Participants will then complete two test trials on each limb, starting again with the unaffected side. The shortest time (seconds) taken to hop the 6-m distance will be recorded.

##### 9-week change in fat mass index

Individuals with a history of knee injury are 4.4 (95%CI 1.6,12.3) times more likely to be in the highest quartile of fat mass index (kg/m2) [10]. Fat mass index will be measured with Bioelectrical Impedance (Taninta Body Composition Analyzer, Model TBF-300A, Tanita Inc., USA) which is feasible method for assessing and tracking body composition in clinical settings. Participants will stand barefoot on the bioelectrical impedance platform during which the resistance to the flow of this single, high frequency alternating electrical current (500A at 50 kHz) will be measured. The device will be calibrated prior to each scan (according to the manufacturer’s protocol).

##### Perspectives of knee injury participants

At study end, knee injury participants will complete an online survey that will ask questions about their SOAR program experience (satisfaction, accessibility). Additionally semi-structured 1:1 interviews will be conducted with a purposive maximum variation (balanced by sex, age, group allocation, time since injury, adverse events and adherence) [76] sample of approximately 15–20 participants. Using an inductive approach and interview guide, interviewees will be asked open-ended queries about their experiences and perceptions of SOAR including self-management, social support and therapeutic relationship. Interview guides have been co-developed with patient partners, and will be piloted and refined during data collection to ensure developing themes are effectively illuminated. Probes and prompts will provide elaboration. Field-notes will be taken, and interviews recorded. Sampling will be informed by ongoing analyses [76]. Data collection will cease when no new themes are identified [77].

##### Perspectives of PT participants

At study end, PTs will complete an online survey of their SOAR program experience (satisfaction, accessibility). Additionally, semi-structured 1:1 interviews will be conducted with a purposive maximum variation (balanced by sex, age, years of practice) [76] sample of approximately 7 PTs. Using an inductive approach and interview guide. Interviewees will be asked open-ended queries about their experiences and perceptions of SOAR, including SOAR and BAP training, and possible implementation clinic processes. Interview guides have been co-developed with patient and PT partners, and will be piloted and refined during data collection to ensure developing themes are effectively illuminated. Probes and prompts will provide elaboration. Field-notes will be taken, and interviews recorded. Sampling will be informed by ongoing analyses [76]. Data collection will cease when no new themes are identified [77].

#### Protocol feasibility outcomes

Protocol feasibility will be assessed with implementation, practicality and acceptability outcomes [32, 39].

*Implementation* outcomes included enrollment rate, participant attrition (% of participants who withdrew or lost to follow-up), protocol adherence (% of intervention and assessment components completed), participant adherence (Exercise Adherence Rating Scale; EARS, Participant Numerical Rating Scale of Action Plan Completion), PT intervention fidelity (% of a 41-item checklist completed during one randomly recorded 1:1 knee camp and one weekly counselling sessions per PT; Table 5, Supplementary File 1 – Intervention Fidelity Checklist), relational empathy (Consultation and Relational Empathy measure; CARE) which is a key component of therapeutic relationship, and change in PT BAP confidence. The EARS is a six-item self-report tool for measuring adherence to home exercise. Scores range from 0 to 42, with higher scores indicating better adherence [78]. The CARE is a 10-item self-report tool that measures empathy in the context of the therapeutic relationship between a clinician and a patient. Scores range from 10 to 50, with higher scored reflecting more empathy [79].

*Protocol Practicality* outcomes included the number of self-reported adverse events (requiring medical treatment or medications, and/or interferes with function for two or more days directly related to SOAR) [80] over the course of the intervention, and exercise-therapy and physical activity goal completion (% of goals entirely, partially or not completed) tracked weekly at the PT counseling sessions.

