### Study design and setting

This is a proof-of-concept, two-armed, open-label, randomized delayed control trial [32] with embedded 1:1 interviews. In this design, randomization determines when the intervention is provided (immediate or 9-week delay). A delayed-control is appropriate as the standard of care after discharge from knee trauma care is no care, and the intervention is beneficial and low risk [33, 34].

The study is guided by the Standard Protocol Items: Recommendations for Intervention Trials, [35] and Standards for Reporting Qualitative Research [36]. Protocol reporting follows the Standard Protocol Items: Recommendations for Intervention Trials, while trial reporting will follow the Consolidated Standards of Reporting Trials statement [37] and Consensus on Exercise Reporting Template [38]. Protocol feasibility assessments will be guided by Bowen et al. [39] and Thabane et al. [32] The research will be conducted at the University of British Columbia (UBC) and Arthritis Research Canada, in Vancouver, Canada between December 2021 and December 2022. The study is approved by the UBC Clinical Research Ethics Board (REB #H21–01491) and all participants will provide informed consent and complete a Physical Activity Readiness questionnaire (PAR-Q,2002) prior to testing [40].

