### Data collection and management

Data will be obtained through questionnaires hosted on a secure online survey platform (REDCap 10.9.4, Vanderbilt University, US). At each testing period knee injury participants will also attend a 1-h in-person laboratory session to complete computerized dynamometry testing of knee extensor and flexor muscle function, and a dual x-ray absorptiometry scan to estimate body mass index and body composition. At the end of the in-person session, participants will be given a triaxial accelerometer and instructed on how to wear it for 7-days. The accelerometer will be returned in a postage paid courier envelope. Secure online forms (Microsoft© Sharepoint) will be used to track knee injury participants attendance, adverse events, healthcare use, exercise/activity goal completion, Rating of Perceived Effort, and any associated pain. Data will be stored in secure electronic databases and de-identified. All authors will have access to the final dataset.

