#### Weekly home-based exercise-therapy, physical activity and activity tracking

At home, participants will work to meet their exercise-therapy and physical activity goals. Degree of exercise-therapy goal completion, Rating of Perceived Effort, and any associated pain will be recorded on the Participant-Tracking form, and physical activity (Fitbit®) data synchronized with the Fitbit® online ‘Dashboard’.

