#### Weekly PT-guided exercise-therapy and physical activity action-planning

Each week knee injury participants will attend a short (~ 15–30) 1:1 virtual PT counseling session and have the option of supplementing their home program with a regularly scheduled one-hour virtual PT-guided group exercise class (Table 3, Supplementary File 1 - Group exercise class menu). At the weekly counselling sessions PTs will ask and record responses to questions related to adverse events, medication and healthcare use, Fitbit® wear, and SMART goal completion on a bespoke PT tracking form. Participants and their PT will progressively modify or add SMART exercise-therapy and physical activity goals (using a BAP approach) based on the past weeks goal completion, physical activity (Fitbit® Dashboard), symptoms and obstacles encountered. At group class, participants will receive added instruction and feedback about exercise performance and progression. Participants will be able to email their PT between sessions as needed.

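### Adverse events, new injuries and healthcare use are not ascertained alike in the two randomised groups between baseline and week 9

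*Protocol article*

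**What the plan says.** All of this is in the protocol article.

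- **Definition and window (Protocol feasibility outcomes).** Adverse events are a practicality outcome. They are self-reported and must need medical treatment or medication, and/or meet a second limb worded "interferes with function for two or more days directly related to SOAR". They are counted "over the course of the intervention, and exercise-therapy and physical activity goal completion", and the sentence ends "tracked weekly at the PT counseling sessions".
- **Who asks (Weekly PT-guided exercise-therapy and physical activity action-planning).** "At the weekly counselling sessions PTs will ask and record responses to questions related to adverse events, medication and healthcare use". The answers go on a physiotherapist tracking form. Participants may also email their physiotherapist between sessions.
- **Forms (Data collection and management).** Online forms "will be used to track knee injury participants attendance, adverse events, healthcare use, exercise/activity goal completion", among other items. The section does not say who completes them.
- **The participant's own form (Weekly home-based exercise-therapy, physical activity and activity tracking).** Goal completion, perceived effort and "any associated pain will be recorded on the Participant-Tracking form". No adverse-event item is named.
- **Timing (Procedures).** The immediate group has sessions in weeks 1–8 and 10–17, the delayed group in weeks 10–17 only. T1, at 9 weeks, is the efficacy endpoint.
- **Rationale (Study design and setting).** The delayed control is justified partly because "the intervention is beneficial and low risk".
- **Analysis (Statistical analyses).** No between-group comparison of adverse events is named.

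**The concern.** From T0 to T1 the trial has a concurrent randomised group receiving no care. That is the only period in which knee flares, re-injuries or treatment-seeking on the programme could be set against a background rate. The population is 12–48 months past a knee injury, so such events can be expected with or without the programme. If one group is asked every week and the other is not asked, and the counting rule covers only time on the programme, that comparison is lost at collection. A later analysis plan cannot recover it.

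Two further consequences follow. Someone who misses sessions or leaves because of a flare loses the scheduled prompts that would have recorded it, so the count probably runs low. And a new injury or new treatment during the wait could affect T1 knee extension torque, the primary outcome. Statistical analyses lists subsequent injury among the potential confounders, but Participant characteristics places its collection on the baseline questionnaire.

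**Working it through.** The protocol gives no expected adverse-event rate and no safety sample size, so there is no figure of its own to reproduce. The check is of who is asked, when, and what counts.

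**Scheduled enquiries, assuming full attendance.** Inputs: 35 per group (Sample size); weekly sessions on the schedule in Procedures. Formula: participants × weekly sessions.

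| Period | Immediate group | Delayed group |
|---|---|---|
| Weeks 1–8 (within T0–T1) | 35 × 8 = 280 | 35 × 0 = 0 |
| Weeks 10–17 (within T1–T2) | 35 × 8 = 280 | 35 × 8 = 280 |

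Enquiry is balanced only after T1, when both groups are on the programme and there is no untreated comparator.

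**Do the online forms close the gap?** The items listed for them are attendance, adverse events, healthcare use, goal completion, perceived effort and pain. These largely match the two programme forms: goals, effort and pain on the participant's form; adverse events, healthcare use and goals on the physiotherapist's. Session attendance and goal completion do not exist for someone who is waiting. The likely reading is that this section says where the programme forms are hosted, but the text does not state it. Either way, a delayed-group event before week 10 falls outside the counting window.

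**Does the ambiguous wording matter?** The phrase about relation to SOAR may qualify both limbs of the definition or only the second. On the narrower reading, an unrelated event needing treatment would count for someone on the programme. It still would not count for someone waiting.

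**What a like-for-like comparison could show.** The risks below are assumptions; the documents give none. For n per group, two-sided α = 0.05 and p̄ = (p1 + p2)/2:

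power = Φ{ (|p2 − p1| − 1.96·√[2p̄(1 − p̄)/n]) / √[(p1(1 − p1) + p2(1 − p2))/n] }

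For 5% v 20% with n = 35: (0.15 − 1.96 × 0.0791)/0.0770 = −0.064, and Φ(−0.064) = 0.47.

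| Assumed risks | 35 per group | 26 per group (35 × 0.75 = 26.25) |
|---|---|---|
| 5% v 10% | 12% | 10% |
| 5% v 20% | 47% | 37% |
| 5% v 30% | 80% | 67% |

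The normal approximation is rough at such small expected counts (0.05 × 35 = 1.75), but the message is clear: the table would be descriptive unless the excess were very large.

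**The case against.** The strongest reply is that nothing is contradicted. Adverse events are a feasibility outcome in a proof-of-concept trial, no randomised safety comparison is promised, and such a comparison would have little power. That stands, and it limits the point to an inexpensive improvement.

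The article is also condensed, and the schedule in Table 1 is not shown. The full protocol may describe another reporting route. That stands as a caution about collection, but not about the counting window, which the article itself states.

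KOOS pain and symptoms and patient-specific function are 9-week outcomes, with mean changes described by study group. So there is some randomised comparison of knee worsening at T1. This stands in part: score changes at one visit can miss transient flares and do not record injuries or treatment.

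A reader might infer more than the text supports:

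- *That only the treating physiotherapist collects adverse events.* The online forms are mentioned without naming who completes them or excluding a group, and email and bi-weekly monitoring meetings also exist.
- *That the waiting group and non-attenders yield no events.* The delayed group contributes in weeks 10–17, and an event missed at one session can be reported later.
- *That events count only if the physiotherapist attributes them to SOAR.* The wording is ambiguous, and nobody is named as judging relatedness.
- *That an upper confidence limit for zero events measures the problem.* Such a limit depends on the number exposed, not on how events are collected, and up to 70 people are scheduled to receive SOAR.

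**Conclusion.** The point holds as a design weakness. On the stated definition and the described questioning, adverse events, new injuries and healthcare use between T0 and T1 are not comparably ascertained: up to 280 scheduled enquiries in the immediate group against none in the delayed group, with waiting time outside the counting window. Participants who miss sessions or drop out are under-ascertained, by an amount the documents do not allow one to estimate.

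The enquiry counts assume 35 per group and full attendance, and that no unseen schedule adds a common question for both groups. If one does, the collection gap narrows, but the window and the ambiguous wording would still need changing. The likely gain is a descriptive background rate and a record of new injury or treatment before the primary endpoint, not a powered safety test.

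**What to change.** 1. Add the same short questions on adverse events of any cause, new injury and healthcare use to the REDCap questionnaires at T1 (covering T0–T1) and T2 (covering T1–T2). Send them to both groups, including people who stopped attending sessions.
2. Redefine the outcome as all events meeting the stated severity criterion in the period, whatever the cause. Record relatedness to SOAR as a separate item, so that the phrase no longer has to be parsed.
3. Tabulate events by randomised group for T0–T1 as a descriptive comparison, with SOAR-related events as a subset. Base this table on the common questionnaire alone, because adding the weekly reports would bring back the unequal enquiry. Keep the weekly reports as a separate listing.
4. State in Data collection and management who completes the online forms and whether they cover the waiting period.

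The cost is a few items at questionnaires already scheduled and one more table. More unrelated background events will be listed. The answers will also rest on about nine weeks' recall by unblinded participants, although the question and recall period would be the same in both groups.

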**Fig. 1 Fig1:**
[figure not shown]
Overview of knee injury participant flow through the study

Figure 2 outlines the study phases for the PT participants. Interested PTs will attend an online information session and then send an email to research team to express their interest. After a videoconferencing interview to confirm eligibility PTs will receive an URL to an electronic consent form located on a data management platform (REDCap 10.9.4, Vanderbilt University, US). After consenting, PT will complete baseline testing (online questionnaires), training and then will be randomly assigned to knee injury participants (see below). PT outcomes will be evaluated prior to training (baseline) immediately after training, and after they have delivered the SOAR program to all knee injury participants that they have been assigned in the study.

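### Goal completion is measured at attended sessions and programme experience at study end, so both figures, read alone, may be too favourable about people who stop

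*Protocol article*

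**What the plan says.** Under Protocol feasibility outcomes, the practicality measures include "exercise-therapy and physical activity goal completion (% of goals entirely, partially or not completed) tracked weekly at the PT counseling sessions". The section on weekly PT-guided action-planning agrees on the source: "PTs will ask and record responses to questions related to adverse events, medication and healthcare use, Fitbit® wear, and SMART goal completion". The same section says where later goals come from: "Participants and their PT will progressively modify or add SMART exercise-therapy and physical activity goals". Knee Camp sets goals for week 1 only.

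There is a second record. In the home-based component, "Degree of exercise-therapy goal completion, Rating of Perceived Effort, and any associated pain will be recorded on the Participant-Tracking form", while physical activity is captured through the Fitbit dashboard. Data collection and management adds that secure online forms "will be used to track knee injury participants attendance, adverse events, healthcare use, exercise/activity goal completion".

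On experience, Perspectives of knee injury participants states: "At study end, knee injury participants will complete an online survey that will ask questions about their SOAR program experience". The interviews in that section are sampled for maximum variation, with adherence and adverse events among the balancing characteristics.

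Attrition (withdrawn or lost to follow-up) and protocol adherence (share of intervention and assessment components completed) are listed as separate implementation outcomes beside goal completion.

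**The concern.** The weekly session is both where goals are scored and where the next ones are made. Once a participant stops attending, no new goals exist, so the remaining weeks leave the numerator and the denominator together. A percentage of goals completed then describes how well people did while they were attending. That is a fair question, but it differs from how much of the planned programme was carried out.

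The survey raises a related problem. Someone who left the programme in week 3 and is first asked about it at study end is less likely to answer than someone who finished, and recall is older.

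These outcomes are meant to inform a future hybrid effectiveness-implementation trial. People who stop because the programme did not suit them are the most informative about practicality and satisfaction, and these two measures reach them least. The survey timing matters more than the denominator, because a survey not sent when someone leaves cannot be recovered in the analysis.

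**Working it through.** The article gives no goal-completion or satisfaction figure to reproduce, so the size can only be illustrated.

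**Inputs**
- c, completion in attended weeks: assumed 80%, range 70–90%.
- d, share of starters who stop: 25%, borrowed from the attrition allowance in Sample size. That allowance concerns loss from the trial, not from the programme, so 10% is shown as well.
- f, share of the 8 planned weeks attended before stopping: assumed 4/8 or 2/8.
- Also assumed: equal numbers of goals each week, the same completion rate before stopping in both kinds of participant, and no goals after stopping.

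**Formulae**
- Share of planned weeks with goals = 1 − d + d × f.
- Completion over planned weeks = c × (1 − d + d × f).
- Gap from the attended-weeks figure = c × d × (1 − f).

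**Results at c = 80%, d = 25%**
- Stop after week 4: 0.75 + 0.25 × 0.5 = 0.875, and 0.80 × 0.875 = 70%. The rest is 17.5% with goals set but not fully completed and 12.5% with no goals.
- Stop after week 2: 0.75 + 0.25 × 0.25 = 0.8125, and 0.80 × 0.8125 = 65%. The rest is 16.25% set but not fully completed and 18.75% with no goals.

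In both cases the attended-weeks figure is 80%.

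**Range of the gap**
- d = 25%, c = 70–90%: 8.75–11.25 points at f = 4/8, about 13.1–16.9 points at f = 2/8, and 17.5–22.5 points in the limit f = 0.
- d = 10%, c = 70–90%: 3.5–4.5 points at f = 4/8 and 7–9 points at f = 0.

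**Number of weeks by group.** Procedures gives the immediate group sessions in weeks 1–8 and 10–17 (8 + 8 = 16) and the delayed group sessions in weeks 10–17 (8). With equal groups, the immediate group's second period makes up 8/24, one third, of all planned session weeks. It lies outside the 8-week programme named in the Aim. This affects the percentage only if all weeks are pooled, which the article does not say.

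**Satisfaction.** Assume 90% satisfied among those who finish and 40% among the 25% who stop. The true figure is 0.75 × 0.90 + 0.25 × 0.40 = 77.5%. If no leaver answers, the survey shows 90%. If all finishers and half the leavers answer, it shows (0.675 + 0.125 × 0.40) / 0.875 = 82.9%.

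**The case against.** The strongest reply is that the plan already counts people who stop. Attrition and protocol adherence sit beside goal completion, and a missed session is an uncompleted component. Goal completion then answers a narrower question, whether goals that were set were achieved, and it is sound to report retention, attendance and conditional completion separately. This stands. A reader might infer that feasibility as a whole is overstated, and the article does not support that.

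A reader might also infer that goal completion is recorded solely from attenders. It is not: participants log exercise-therapy goal completion themselves, and online forms track goals and attendance. What remains is that a form can score only goals that exist, and the practicality outcome names the session as its source.

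The survey is likewise not restricted to completers. Stopping the programme is not leaving the study, and an online survey needs no attendance. The risk is non-response, not a stated exclusion. Interviews sampled across adherence help in understanding why people stop, but 15–20 interviews do not correct a percentage.

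A further tempting reading concerns physiotherapists, whose last outcome time point comes "after they have delivered the SOAR program to all knee injury participants that they have been assigned in the study". That fixes when their outcomes are measured. Their experience survey is separately timed at study end, with no condition that they finish all assigned participants, so it gives no ground for the same criticism.

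Finally, the exact denominator and the pooling of weeks are details that an article may leave to the full protocol or analysis plan. Their absence is not the point here. The point rests on the stated source and timing.

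**Conclusion.** The point holds in a limited form. As described, the goal-completion percentage is conditional on continued attendance, and the satisfaction figure is open to non-response from people who stop. Read alone, either may be too favourable. Under the assumed 80% completion and 25% stopping, completion over planned weeks would be 65–70% instead of 80%. The gap shrinks to about 4 points if 10% stop halfway (0.80 × 0.10 × 0.5 = 0.04). None of these percentages is a result of the trial or can be derived from the article.

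Nothing here touches the primary outcome or its analysis. Severity is minor: two inexpensive improvements to measures that will be used to plan the next trial.

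**What to change.** 1. Send the existing online experience survey when a participant who has started the programme discontinues it, as well as at study end, and report the response rate. This has to be arranged prospectively.

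2. Report goal completion per participant who started, over the 8 planned programme weeks, using both the PT and the participant tracking forms. Show weeks without a session or without goals as a separate category; do not score them as failed, since a participant may have exercised and logged it while missing a call. Restricting to starters keeps delayed-group participants lost during the waiting period from being counted against goals they never set. Report the immediate group's weeks 10–17 separately, and keep the conditional figure beside attrition.

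The cost is an added trigger for a survey that already exists and a fuller table. The reported figures may look slightly less favourable, and some leavers will still not respond.
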